## Abstract

**Background:**

The resource group method provides a structure to facilitate patients’ empowerment and recovery processes, and to systematically engage significant others in treatment and care. A patient chooses members of a resource group (RG) that will work together on fulfilling patients’ recovery plan. By adopting shared decision-making processes and stimulating collaboration of different support systems, a broad and continuous support of patients’ chosen goals and wishes is preserved and problem solving and communication skills of the RG members are addressed.

**Objective:**

The objectives of this study are (1) to establish the effectiveness of the RG method in increasing empowerment in patients with severe mental illnesses (SMI) in the Netherlands; (2) to investigate the cost-effectiveness and cost utility of the RG method; and (3) to qualitatively explore its dynamics and processes.

**Methods/design:**

This multisite randomized controlled trial will compare the effects of the RG-method integrated in Flexible Assertive Community Treatment (FACT) (90 patients) with those of standard FACT (90 patients). Baseline assessments and 9-month and 18-month follow-up assessments will be conducted in face-to-face home visits. The primary outcome measure, empowerment, will be assessed using the Netherlands Empowerment List (NEL). The secondary outcomes will be quality of life (MANSA); personal, community and clinical recovery (I.ROC); general, social and community functioning (WHODAS 2.0); general psychopathological signs and symptoms (BSI-18); and societal costs (TiC-P). An economic evaluation of the cost-effectiveness and cost utility of the RG method will also be conducted. A qualitative multiple case-study will be added to collect patients’, RG members’ and professionals’ perspectives by in-depth interviews, observations and focus groups.

**Discussion:**

This trial will be the first to study the effects of the RG method on empowerment in patients with SMI. By combining clinical-effectiveness data with an economic evaluation and in-depth qualitative information from primary stakeholders, it will provide a detailed overview of the RG method as a mean of improving care for patients with SMI.

*Trial registration* The study has been registered in the Dutch Trial Register, identifier: NTR6737, September 2017.

## Introduction

Traditionally, severe mental illnesses (SMI) were seen as chronic diseases with relapsing or deteriorating symptoms and poor prognoses [1, 2]. Recovery was perceived as a medical outcome defined by remission of mental health symptoms [3]. Due to the consumer movement, a new view emerged in psychiatry in the 1990s [4, 5]. Within this view, recovery is conceptualized as a unique, personal and ongoing process of growth that involves learning to live with one’s disability despite the limitations of symptoms, and gradually rebuilding a sense of purpose, agency, and meaning in life [5–7].

This conceptualization of recovery was incorporated within the development of new working models for organizing mental healthcare. One of these models is Flexible Assertive Community Treatment (Flexible ACT) [8] that was established in the Netherlands as a Dutch variant of Assertive Community Treatment (ACT) [9]. Flexible ACT teams deliver services for an entire group of people with SMI in a particular region by adapting a flexible switching system between standard community mental healthcare and an intensive ACT equivalent [8, 10]. This combination of flexibility and continuity of care provides opportunities for combining recovery-oriented care with evidence-based medicine, best practices and integrated community and hospital care.

However, an examination of the model fidelity of FACT teams between 2009 and 2014 showed that support of recovery, rehabilitation and participation was implemented insufficiently [11]. Similar findings were shown by a nationwide survey in 2016, which reported that over 80% of patients with SMI experienced feelings of loneliness, that 40% did not feel that they were part of society, and that only 20% had paid or unpaid employment [12]. Second, although the informal support system is perceived as an important factor in supporting recovery and participation and the effectiveness of involving significant others in SMI care is well established, it has been found that systematic and formal forms of support and contact with family members are seldom achieved [3, 11, 13, 14]. These implementation problems justify the ongoing search for a mental health service that empowers patients with SMI, by stressing their choice and autonomy and by encouraging social connectedness and participation.

A structured method for reinforcing empowerment and social connectedness in mental healthcare is represented by the resource group method. In short, to constitute a resource group (RG), patients nominate significant others from their informal network (such as friends and family) and their formal network (such as a social worker or job-coach). During the frequent RG meetings, the RG discusses patients’ goals and wishes, and jointly determines a recovery plan to achieve them.

The first important characteristic of the RG method is that patients themselves take the lead in any decisions: they nominate the members of their RG, set their recovery goals and determine important aspects of how the RG meetings are designed [15]. Considering these decisions is a crucial factor in patients’ sense of autonomy and sense of ownership of their treatment. Patients are then encouraged to extend this to autonomy and ownership of their illness (such as their ability to cope with symptoms) and regarding other social and community aspects of life. This process of regaining control over one’s life—despite the need for support—is a key concept of empowerment, and is regarded as an important driving force in recovery [16, 17].

The second important characteristic of the RG method is that significant others are systematically engaged in treatment and care [18]. As a patient and his or her significant others form a team together with involved professionals, support in the recovery plan is broadened. Hereby, the fulfillment of a meaningful life and everyday activities is strengthened. In other words, through collaboration—joint discussion of patients’ wishes and needs, and creating space for sharing experiences and emotions—an empowered and supportive social environment can be built to supplement professional care. Having such environment in turn, is assumed to foster resilience and continuity in social and community integration. Improved integration and a feeling of connectedness are seen as facilitators and indicators of recovery [1, 19–21].

Also, it is increasingly recognized that significant others need social support to break isolation and reduce stigma [22, 23]. Moreover, studies investigating experiences with care report that families feel marginalized, uninformed, lack a recognized role and distanced from the care planning process [24–26]. Therefore, a structured and more frequent contact between professionals and significant others would meet with their need to feel more part of the treatment and care. Additionally, professional support and attention to the consequences of the patients’ disease for the personal wellbeing of the important people around the patient, may reduce their burden, increase their sense of security, and improve their own mental health status [13, 27, 28]. Moreover, during the RG meetings all involved professional caregivers from different sectors (e.g., mental health, social affairs, housing and employment) can be invited. In this way, the RG method responds to the need to improve communication between all those involved, pursuing a consistent and collaborative model of integrated care.

In sum, the RG method structures the care and support that is built around patients’ personal choices, wishes and aspirations. It focuses on creating a mental health system that encourages patients to be active, informed and autonomous participants who, by collaborating with their social environment, can develop the support that meets their needs and chosen lifestyle. By systematically engaging patients’ significant others, continuity in support is embedded. Eventually, it is hoped, a resilient, empowered social support system can be created that functions independently of professional resources. As the RG method thus has great potential for promoting the autonomy, empowerment and recovery of patients with SMI, it may bring valuable improvements to standard FACT. The origins of the RG method lay in the Optimal Treatment (OT) model, which integrates biomedical, psychological and social strategies in the management of SMI [29, 30]. It was shown in a meta-analysis of the effectiveness of variations of the OT model for patients with a psychotic disorder (N = 2263, 6 randomized studies, 11 observational studies, follow-up between 12 and 60 months) that participation in the OT model led to clinically significant improvements. Relative to care as usual, it improved functioning (Cohen’s *d *= 0.82), increased well-being (*d *= 0.88) and reduced symptoms (*d* = 0.72) [31]. Similarly, a systematic review of eight RCTs showed that the OT program improved symptoms, functioning and well-being in patients with a psychotic disorder [18]. In Sweden, the “family unit in the community” was regarded as a central element of the OT model, and was further developed as the concept of the “resource group” [32]. To reflect the key role of the RG and to integrate it into the existing mental healthcare programs for patients with SMI, the Swedish OT program was relabeled as Resource Group Assertive Community Treatment (RACT) [33, 34]. In this way, ACT teams [9] were enriched and augmented by resource groups involving patients and their network in clinical case management by shared decision making procedures.

This study is intended to add to the existing research in three ways. First, in the studies included in the meta-analysis and review referred to above, integrated care models related to the RACT program were assessed. However, no study has investigated the specific additional value of the RG method in a head-to-head comparison with FACT. Second, previous studies focused on patients with psychotic disorders. Knowledge is lacking about the effectiveness of the RG method for patients across the entire psychiatric spectrum. The third contribution is intended to provide in-depth understanding of the meaning of the experiences in using the RG method to those involved. Very few qualitative contributions have been conducted. As most focused mainly on the case-managers’ point of view [33], they overlooked the experiences and perspectives of patients, RG members and other professionals. To better understand the RG method and its implementation, we thus intend to conduct exploratory research that analyses its dynamics and meaning from the perspectives of those involved.

To achieve these objectives, this study consists of a randomized controlled trial (RCT) to establish clinical effectiveness, an economic evaluation and a qualitative case study on the dynamics, meaning and implementation of the RG-method. The primary objective of the study is to determine whether the RG method integrated in FACT is more effective in empowering patients with SMI when compared to standard FACT. Secondary objectives consist of the assessment of the RG method in improving quality of life and enhancing social and community functioning; and, in an economic evaluation, to investigate its cost-effectiveness. An add-on qualitative study will explore the perspectives of those involved and the implementation of the RG method in Dutch mental healthcare.

## Methods

This three-part study will consist of an effectiveness study, an economic evaluation and a qualitative case study. The study protocol was written in accordance with the CONSORT guidelines [35].

### Part one: effectiveness study

#### Study design

Patients in this multisite RCT will be randomly allocated either to RG method plus FACT or to standard FACT (ratio 1:1). Randomization will be performed at individual patient level. Data for both conditions will be collected at baseline and after 9 and 18 months (follow-up assessments). For an overview of the flow of screening procedures and assessments, see Fig. 1. Importantly, since FACT teams do almost all outpatient care in the Netherlands for SMI patients, it was not possible to have a second control group without FACT.

**Fig. 1 Fig1:**
[figure not shown]
Flow chart of study design. *FACT* Flexible Assertive Community Treatment, *RG* resource group

#### Study population

The study will be conducted within the context of community-based outpatient psychiatric care for people with SMI. In the Netherlands, FACT [8] is the used service-delivery model for the care and treatment of people with SMI (see “Interventions” for a description of FACT). The target population consists of patients who meet the criteria for the Dutch definition of people with SMI who receive FACT.

##### Inclusion criteria

The inclusion criteria for the study are consistent with the general inclusion criteria for FACT. That is, patients will be eligible if (1) they are aged between 18 and 65 years, (2) are expected to have FACT for > 12 months, and (3) suffer from a SMI according to the Dutch consensus definition [36]. For the latter, individuals must meet the following five criteria, in which:They have a psychiatric disorder which requires care and treatment (≈ are not in symptomatic remission);They have severe limitations in social and community functioning (≈ are not in functional remission);These two criteria are interrelated, with the limitations being the cause and consequence of the psychopathology.These problems are not transient in nature (i.e., they are systematic and long-lasting).The treatment plan requires coordinated care provided by integrated networks of health practitioners.

##### Exclusion criteria

Patients are not eligible if (1) their knowledge of Dutch is not sufficient for them to understand and read the questionnaires; and if (2) they are unable to understand and sign the informed consent form.

#### Hypotheses and research questions

Hypothesizing that FACT plus RG is a helpful intervention for patients suffering from SMI by improving their empowerment and strengthening their support sources, we state the following research questions:Does RG plus FACT increase the empowerment of patients with SMI more effectively than standard FACT?Does RG plus FACT improve these patients’ quality of life and satisfaction with care, and enhance their social and community functioning more effectively than standard FACT?

#### Study procedures

##### Recruitment

Patients will be recruited at nine mental healthcare organizations throughout the Netherlands, each of which will participate with minimum two FACT teams. Care providers of the FACT team will screen patients on the basis of the inclusion and exclusion criteria (see Fig. 1). After informing eligible patients of the RG procedures and the study, care providers will then ask them to participate. To this end, patients will receive oral and written information about the RG model and an information letter outlining the trial procedures, explaining confidentiality, and providing the contact details of the research team. Interested patients will be given a week to consider their participation.

The above described procedure for screening and informing patients about the study will be performed on two different groups of patients: either new patients entering a FACT team (i.e., during the intake phase); or a randomly generated selection of patients who have already been in FACT for no more than 24 months. For the latter, we will use an online tool (http://www.randomizer.org), to randomly select patients who have been recently (24 months) added to the caseload of the case-managers trained in the RG method. Importantly, these two routes are used to screen and inform a representative sample of the FACT population of the study. After patients sign informed consent, the researcher will perform an extra check on the inclusion and exclusion criteria and an independent interviewer will contact the participant to make the first appointment for the baseline assessment. After completing the assessment, participants will receive a gift voucher worth €15,-.

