##### Randomization and blinding

Randomization will be performed on an individual level. A statistician from the Trimbos Institute, who will be independent from the research team, will perform the randomization using a computer-generated concealed-randomization sequence stratified on teams. To keep randomization unpredictable, the sequence will contain variable-allocation block sizes [37], in which two sizes of allocation blocks (i.e., 2 and 4) are randomized. Assuming ten participants per team, this results in three possibilities for block size 4 (i.e., 2 × 4; 1 × 4; 0 × 4). To minimize the risk of imbalance between conditions, the ratio of these sequences will be stratified on respectively 1:2:2. The allocation sequence will be stored by the independent statistician and be concealed from all researchers, care providers and participants. Participants will be allocated after baseline measurement. Once they have been allocated, the researcher and local staff will be informed of the condition by email. Further matching between patient and case-manager will be performed by the local FACT team staff and will be based on condition. That is, when participants are allocated to the RG condition, care providers trained in the RG procedures will be the case-manager. Patients in the control condition can have any FACT care providers as their case-manager.

Assessments comprise self-report questionnaires, and structured and semi-structured interviews (see Table 3). They will take place at the participants’ homes or any other location they prefer. An independent and blinded interviewer will guide them through the self-report questionnaires and will conduct the interviews. The interviewer will bring a laptop and- using a unique login-code- will assess the questionnaires online, then securing them on an encrypted server (Jambo). If participants are unable to use the laptop, they will fill in the questionnaires on paper and the interviewer will then later enter the data into the online environment.

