##### Standard Flexible Assertive Community Treatment (FACT) (for a more comprehensive description, see [38])

FACT is a rehabilitation-oriented outpatient clinical case management model for patients with severe mental illness. Integrated care and support is provided in the patients’ own environment by a multidisciplinary team of professionals (e.g., psychiatrist, psychologist, nurses, social worker, job coach and peer specialist). On average, a FACT team consists of 11–12 professionals that monitor 200 patients [38]. The FACT model is characterized by its flexible switching between two types of care, according to patients’ needs:*Individual case management for more stable patients.* The case-manager visits a patient 2–4 times a month at his/her home or elsewhere and is responsible for the individual care and treatment plan. This plan is renewed at least once a year and is formulated in a way that patients and their families can understand. Part of this plan can be a so-called crisis plan, which describes early-warning symptoms and concrete arrangements for intensifying care if necessary. Appointments with the psychiatrist (for management and evaluation of medication) and with the psychologist (for psycho-education or cognitive behavior therapy) can take place at the FACT center or at the patients’ home. On indication, family interventions and supported employment may be added to the treatment plan.*Shared case management and intensive assertive outreach care for unstable patients who are at risk of relapse, neglect or readmission*. The care for the individual patient is intensified but performed by the same team. That is, this group of patients is discussed daily during the team meeting using the digital FACT-board (DigiBoard); the psychiatrists sees the patient within 2 days; the crisis plan is updated and set in motion; and the case-manager informs the patient (and if necessary the family) that more intensive care will be organized and that colleagues from the FACT team will work together to prevent readmission and to shorten the crisis. If the crisis or risk of relapse has decreased and the situation has stabilized, the care is shifted back to individual case management.

To date, the effects of FACT have not been studied in the context of an RCT. Uncontrolled studies have shown a pre-post effect on symptoms and admissions [10, 39–41].

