#### Analyses

Outcome data will be analyzed using multilevel mixed regression models with 4 levels: observations within people, people within teams, and teams within centers. Analyses will be conducted on the entire randomized sample (i.e., intention to treat). Supplementary analysis will be done on the completers sample. A completer will be defined after further inspection of the frequency of the RG meetings to define a minimum of attendance of a RG meeting during a 12-month period after the first assessment. In future publications the number of minimum RG meetings will be clearly stated within the definition of a completer and included in the consort flow chart of the RCT. To analyze potential between-condition differences in baseline characteristics (such as gender and diagnosis), we will use Student’s t-tests for continuous variables and Pearson Chi-squared tests for categorical variables. As a covariate, the analysis will include variables that show different distributions in the conditions (p ≥ 0.05 difference at baseline) and are correlated with the results. For categorical outcome variables we will choose counts and, if there are non-normal residuals, appropriate forms of mixed regression (such as binomial, Poisson and gamma). All analyses will be carried out using SPSS version 20+ and/or R version 3.0+. Results will be described in accordance with the CONSORT guidelines for randomized controlled trials [35].

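### Recruitment route (new to FACT versus already in FACT) is a known design factor, but the covariate rule would usually leave it out of the NEL model; prespecify it as a fixed effect

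*Protocol article*

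**What the plan says.** All references are to the protocol article.

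- **Recruitment.** Two groups are screened: "either new patients entering a FACT team (i.e., during the intake phase); or a randomly generated selection of patients" in FACT for no more than 24 months. The second group is drawn at random from patients recently "added to the caseload of the case-managers trained in the RG method". The stated aim is that "these two routes are used to screen and inform a representative sample of the FACT population of the study". No share or cap is set for either group.
- **Study design; Randomization and blinding.** Patients are "randomly allocated either to RG method plus FACT or to standard FACT (ratio 1:1"), using a "computer-generated concealed-randomization sequence stratified on teams". Team is the only stratum.
- **Analyses.** The outcome model is described as "multilevel mixed regression models with 4 levels: observations within people, people within teams, and teams within centers". Route and time in FACT are not named. A variable becomes a covariate if its distribution differs between the conditions at baseline (the threshold is printed as p ≥ 0.05) and it correlates with the results.
- **Interventions.** On standard FACT, the text says "Uncontrolled studies have shown a pre-post effect on symptoms and admissions". Table 1 says that standard FACT already invites the social network at intake.

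**The concern.** The two groups meet the trial at different points in care. For a patient at intake, both arms start FACT during follow-up, and RG is added to that start. For a patient already in FACT, RG is added to running care. That patient must also still meet the not-in-remission criteria after up to 24 months of FACT. It is plausible that the course of NEL over 18 months differs between the groups in both arms. The contrast with RG may differ too, because standard FACT has its own network contact at intake.

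Two things are at stake. First, if route predicts NEL change and is not in the model, its variance stays in the error term and the interval for the RG effect is wider than it need be. Second, if the RG effect differs by route, the single pooled estimate averages two effects with weights that nobody planned.

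The covariate rule does not solve this. It asks whether route happens to be unbalanced between arms, which under randomisation is a matter of chance. The gain from adjusting depends mainly on how strongly route predicts outcome, and a balanced but prognostic factor is worth adjusting for.

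**Working it through.** **Inputs from the document (Sample size; Study design).** Two-sided alpha 0.05, power 80%, d = 0.5, N = 126 before further adjustment, N = 133 after allowing for repeated measures and clustering, within-person correlation 0.6, dropout 35%, recruited N = 180, ratio 1:1.

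**Inputs assumed, because the document does not give them.** The share of new patients is q = 0.5. The gap D, in outcome SD, is the difference in NEL change between routes, the same in both arms; it is shown from 0 to 0.8. Clustering is ignored in the steps below.

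**1. The plan's own figure.** N = 4 × (1.96 + 0.84)² / 0.5² ≈ 126. It reproduces (128 with the t distribution).

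**2. How often the covariate rule would admit route.** Arms are formed at random, so a 5% baseline test flags route in about 1 trial in 20, however prognostic route is. In the other 19 it is left out.

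**3. Residual variance without route.** With baseline NEL in the model and correlation 0.6, the residual variance is 1 − 0.6² = 0.64. An omitted binary factor adds D² × q(1 − q). The equivalent number of patients is 180 × added / (0.64 + added).

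| D (SD) | Added variance | Rise in residual variance | Rise in SE | Equivalent patients of 180 |
|---|---|---|---|---|
| 0 | 0 | 0% | 0% | 0 |
| 0.3 | 0.0225 | 3.5% | 1.7% | 6 |
| 0.5 | 0.0625 | 9.8% | 4.8% | 16 |
| 0.8 | 0.16 | 25% | 11.8% | 36 |

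If the residual SD is taken as 1 without the baseline reduction, and D is measured against total variance, the rise is smaller: 1/(1 − q(1 − q)D²) − 1 = 2.3% at 0.3 SD and 6.7% at 0.5 SD (1.9% and 5.5% with a 30:70 split).

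**4. Power at the planned effect.** With 35% dropout, 180 × 0.65 = 117 patients remain. At d = 0.5 and residual variance 0.64, power is 0.92 with route in the model. Without it, power is 0.91 (D = 0.3), 0.89 (D = 0.5) and 0.85 (D = 0.8). It stays above 80% throughout.

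**5. Chance imbalance in route.** With 90 per arm, the SD of the difference in route share is √(2 × 0.25/90) = 0.075, so the 95% range is about ±15 percentage points. At D = 0.5 the far end of that range moves the estimate by 0.146 × 0.5 = 0.07 SD. This is random error and already part of the variance in step 3. It is neither bias nor an extra loss.

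**6. Dependence on the mix.** Pooled effect = q × d(new) + (1 − q) × d(existing). Purely as an illustration, take 0.6 SD in new and 0.4 SD in existing patients. With 20% new patients the pooled effect is 0.2 × 0.6 + 0.8 × 0.4 = 0.44 SD; with 80% it is 0.56 SD. At N = 133 and SD 1, power is 72% and 90% respectively. If the two effects are equal, the mix does not matter.

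**7. Power for a difference in effect between routes.** With equal-sized routes, the SE of the interaction is twice that of the main effect: 2 × √(4/133) = 0.347 at SD 1. For a difference of 0.5 SD, 0.5/0.347 − 1.96 = −0.52, which is a power of about 30%.

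**The case against.** The strongest objection is that this is silence, not error. Covariate lists are often left to an analysis plan, which is not shown, and a journal article condenses. That would settle the matter if the article said nothing about covariates. But it states a selection rule, and the objection here is to what that rule does with a factor known at screening. The rule could admit route, so it would be wrong to say that route is excluded; it is only not prespecified. The printed threshold, p ≥ 0.05, read literally, does not select variables that differ between arms, so it gives no firmer assurance that route enters.

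Three further objections stand and limit the point.

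- **Route is not shown to be prognostic for NEL.** A reader might infer that from the pre-post findings on FACT. Those studies were uncontrolled, concern symptoms and admissions, and do not compare patients by time in FACT. The introduction also reports that FACT teams implemented recovery support insufficiently, which gives no reason to expect a large change in empowerment from FACT alone.
- **The trial is not underpowered because of this.** At the planned d = 0.5, power stays at 0.85 or more without route, even at a gap of 0.8 SD, which exceeds the assumed treatment effect.
- **The pooled effect answers a legitimate question.** The research questions concern patients with SMI in FACT overall, and the existing-patient route uses random selection under a 24-month limit. No document shows that the RG effect differs by route.

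Route is also a coarse marker: a patient one month into FACT is grouped with one at 23 months.

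**Conclusion.** The point holds as a low-cost improvement. Two groups at different points in care are pooled without a planned split, team is the only stratum, and the stated covariate rule would usually omit route when it is prognostic but balanced.

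A reader might infer that the RG estimate is biased or that precision is certainly lost. The documents support neither. Randomisation within team protects the comparison, and any loss depends on a gap that is not given. Under a 50:50 split and residual variance 0.64, the loss is nil at a gap of zero, small at 0.3 SD (3.5% of residual variance) and moderate at 0.5 SD (about 10%). The dependence of the pooled effect on the mix is likewise conditional: it arises only if the RG effect differs by route.

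**What to change.** In the Analyses section, prespecify recruitment route (new at intake versus already in FACT), with its interaction with visit, as a fixed effect in the NEL model and the secondary-outcome models, whatever the baseline comparisons show. Report the share of each route per arm. Give the RG effect by route with 95% CIs, labelled exploratory, because power to detect a difference between routes is low (about 30% for 0.5 SD).

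Leave recruitment and the team-stratified randomisation unchanged. Adding route as a stratum would give 18 × 2 = 36 strata with 180/36 = 5 patients each on average, so a model term is more workable.

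The cost is one or two degrees of freedom and a short addition to the results tables. Route is known for every patient at screening, so no new data are needed. The route-specific estimates will be imprecise and should be presented as such.
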